## Results/Outcomes

### Primary Outcome Measure

The primary outcome of interest in the proposed study is the participant's BDI score at 6 weeks postpartum. The BDI is widely accepted and will be used to measure the severity of depressive symptoms during pregnancy and in the postpartum period. It was first introduced by [name] and colleagues in 1961 (BDI-I) and consists of 21 questions about how the participant was feeling in the last week[35]. Each set of at least four possible answer choices range in increasing intensity. The questions touch on depressive symptoms such as hopelessness and irritability, cognitions such as guilt or feelings of being punished, as well as physical symptoms such as fatigue, weight loss, and lack of interest in sexual intercourse.

The test characteristics of the BDI as a depression screen among pregnant populations have been well-characterized[36,37]. In a longitudinal study among 105 pregnant women attending an urban antenatal clinic, Holcomb found the BDI to be a rapid and sensitive screening test for depression[37]. The standard cutoffs for the BDI are as follows: 0-9 for no significant depressive symptoms; 10-19 for mild to moderate depression; 20-29 for moderate to severe depression; and 30-63 for severe depression. Higher total scores indicate more severe depressive symptoms. The BDI has been used widely in clinical research and especially in pregnant populations[37-39] and has high internal consistency[40]. The questionnaire takes no more than 10 minutes to complete and is prepared at a 5^th ^to 6^th ^grade reading level.

For the proposed study, the BDI will be administered at baseline, 26-28 and 34-36 weeks gestation, and at 6 weeks postpartum. As our primary outcome of interest, depressive symptoms will be measured as a continuous variable and reported in descriptive and multivariable analyses as means and standard deviations.

### Secondary Outcomes

Secondary outcomes we will evaluate include a) the need for depression-related treatment and antidepressant medication during and after pregnancy; b) depressive symptoms, as measured by the BDI, at 26-28 and 34-36 weeks gestation; c) changes in omega-3 fatty acid concentrations in maternal plasma at baseline (<20 weeks gestation) and at 34-36 weeks gestation; d) changes in levels of proinflammatory cytokines (IL-1β, IL-6, and TNF-α ) at baseline and at 34-36 weeks gestation; and e) standard obstetric outcomes including length of gestation, birth weight, Apgar score, mode of delivery, blood loss at delivery, gestational hypertension, gestational diabetes, and preeclampsia. Neonatal outcomes, including cord umbilical pH, length of stay, NICU admission, and antibiotic administration will be recorded as well. We will also evaluate the effect of maternal omega-3 fatty acid supplementation on cord blood fatty acid levels as well as fetal synthesis of proinflammatory cytokines IL-6, IL-1β, and TNF-α.

Information on pregnancy outcomes will be extracted from the electronic medical record. Preterm birth will be defined as delivery before 37 completed weeks' gestation and post-term gestation will be defined as delivery at or beyond 42 completed weeks' gestation. Birth weight, Apgar scores, mode of labor onset (spontaneous or induced), mode of delivery, and estimated blood loss at delivery are all available in the electronic record. Blood loss at delivery is routinely estimated by the delivering physician or midwife. Gestational hypertension will be defined as systolic blood pressure (BP) elevation ≥30 mm Hg or diastolic BP elevation >15 mm Hg compared to early pregnancy BP. Preeclampsia will be defined by blood pressure criteria noted above plus >1+ proteinuria on urine dipstick or > 300 mg protein on 24 hour urine collection. Gestational diabetes will be diagnosed based on a 1 hour glucose after a 50 gm glucose load of ≥200 or 2 abnormal values on a 3 hour glucose tolerance test.

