### Other Planned Exploratory Analyses

To evaluate the effect of fish oil supplementation on omega-3 fatty acid concentrations in maternal blood, we will use a mixed effect model for longitudinal data because the omega-3 fatty acid concentrations will be measured twice for each participant (at baseline and at 34-36 weeks gestation). Using this model, we can assess both the time averaged difference in the concentration between the three groups as well as the change in the concentration over the two measurement times between the three groups. To evaluate the effect of fish oil supplementation on the proinflammatory cytokines referenced, we will use a mixed effect model for longitudinal data because each proinflammatory cytokine level will be measured twice for each participant (at baseline and at 34-36 weeks gestation). Using this model, we can assess both the time averaged difference in the levels between the three groups as well as the change in concentration over the two measurement times between the three groups. To evaluate the effect of fish oil supplementation on standard obstetrical outcomes including but not limited to length of gestation, birth weight, Apgar score, mode of delivery, blood loss at delivery, and preeclampsia, we will use multiple regression for continuous outcomes variables and logistic regression for dichotomous outcome variables, and in either of these approaches, an indicator for fish oil supplementation will be the primary independent variable.

The exploratory aims are intended to generate preliminary data elucidating the possible mechanism of action of fish oil supplementation in the prevention of depression in pregnancy and the postpartum period. In particular, the role of fish oil in inhibiting production of proinflammatory cytokines may provide an explanation for the observed link between depression in pregnancy and preterm birth, a condition known to be associated with inflammation. Although we will be unable to definitively explore these relationships in the proposed study, we intend for these aspects of the study design to generate preliminary data which will allow us to refine our dosing, expected effect sizes, and hypotheses for a larger, multicenter study of the effectiveness of fish oil in prevention of major depression in pregnancy and postpartum.

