## Discussion

The proposed study will assess the effect of two fish oil supplements on depressive symptomatology in an at-risk population through a randomized controlled design. Strengths to this study include its double-blind, placebo-controlled design and its inclusion of two intervention groups to test both an EPA-rich and a DHA-rich supplement. To our knowledge, the proposed study is the first to directly compare these two fish oils in a pregnant population. Results of previous systematic reviews indicate that differences in fish oil composition may account for the heterogeneity of the observed results of prevention and treatment trials for depression[29,30]. However, this hypothesis has not been previously tested in a RCT comparing both interventions.

The proposed study has the potential to impact clinical care for pregnant women at risk for depression during and after pregnancy. There is a significant burden of disease associated with major depression, and although depression during and following pregnancy occurs at a frequency similar to preeclampsia (5-8%) and preterm birth (11%), it receives much less clinical attention. The disability associated with depression is as great as the disability of other chronic diseases such as hypertension, diabetes, and rheumatoid arthritis[44]. Maternal depression during pregnancy may also constitute a risk factor for suboptimal neurobehavioral development of the child. Dietary supplementation with molecularly distilled omega-3 fatty acid preparations may provide a safe and well-tolerated means for pregnant women to reduce their risk for depression.

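### Gestational hypertension is defined by a rise from early-pregnancy blood pressure with no absolute level, so the rule misclassifies women in both directions and dilutes any effect on that outcome

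*Protocol article*

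**What the plan says.** In the protocol article, Secondary Outcomes lists "gestational hypertension, gestational diabetes, and preeclampsia" among the obstetric outcomes.

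- **Gestational hypertension** is fixed as "systolic blood pressure (BP) elevation ≥30 mm Hg or diastolic BP elevation >15 mm Hg compared to early pregnancy BP". The two limbs are joined by "or", so either rise is enough. No absolute pressure is named, and the text does not say which reading is the early-pregnancy value.
- **Preeclampsia** takes over that criterion and adds a urine finding: "Preeclampsia will be defined by blood pressure criteria noted above plus >1+ proteinuria on urine dipstick or > 300 mg protein on 24 hour urine".
- **Source:** "Information on pregnancy outcomes will be extracted from the electronic medical record".
- **Analysis:** Other Planned Exploratory Analyses assigns obstetric outcomes to regression on an indicator for fish oil, with "logistic regression for dichotomous outcome variables". Its non-exhaustive list names preeclampsia but not gestational hypertension. The same section says the exploratory aims cannot settle these relationships and are meant to inform effect sizes and hypotheses for a larger multicentre study.

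The article gives no expected rate, effect size or power for gestational hypertension. The only related rate is 5-8% for preeclampsia, in the Discussion.

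**The concern.** A condensed article may leave abstraction detail to a fuller document. Here, though, it states the case definition itself, and the stated rule measures change, not level. A woman with a low early pressure can meet it without leaving the normal range. A woman starting in the upper normal range can become hypertensive without meeting it.

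False cases unrelated to treatment add the same background to every arm and pull a ratio estimate towards 1, whether the true effect is benefit or harm. These outcomes are meant to supply effect estimates for planning a later trial. A wide confidence interval shows its own imprecision, but misclassification bias does not show in the interval and does not shrink with more women.

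**Working it through.** **1. The plan's own figures.** The only sample-size figure concerns the Beck Depression Inventory. Means 8.4, 4.2 and 4.2 give a variance of means of 3.920; 3.920/6.4² = 0.0957; 35 per group gives 80.5% power. It reproduces and does not bear on this point. There is no plan figure for gestational hypertension to reproduce.

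**2. The rule applied to single women** (arithmetic only; 140/90 is used here as an assumed reference level and is not in the documents).

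| Early to late | Systolic rise | Diastolic rise | Case under the rule? | Late reading at or above 140/90? |
|---|---|---|---|---|
| 100/58 to 114/74 | 14 | 16 | Yes (16 > 15) | No |
| 100/60 to 130/70 | 30 | 10 | Yes (30 ≥ 30) | No |
| 125/76 to 150/90 | 25 | 14 | No | Yes |

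**3. How often false positives could occur (assumed inputs).** Mean early pressure 110/68; between-woman SD 10/8; mean late rise 5/5, 8/7 or 10/10; reading-to-reading SD 6/5, 8/6 or 10/7; correlation 0.5 between systolic and diastolic reading error; one early reading. Share of women with all late readings below 140/90 who meet the rule, lowest to highest across scenarios:

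- one late reading: 7% to 29%;
- any of three late readings: 17% to 52%;
- at least two of three late readings: 5% to 27%.

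A hand check on the diastolic limb alone, before restricting to women below 140/90, uses P = 1 − Φ((15 − rise)/(SD × √2)). Rise 5 and SD 5: 1 − Φ(10/7.07) = 0.079. Rise 10 and SD 7: 1 − Φ(5/9.90) = 0.307. These agree with the ends of the one-reading range. The last bullet shows that a confirmatory reading alone does not remove the problem if no absolute level is set.

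**4. Dilution for gestational hypertension.** Observed rate = p + (1 − p) × f, where f is the false-positive rate, equal across arms, and no true case is missed. Assumed true rates are 8% and 4% (risk ratio 0.50).

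| f | Control | Fish oil | Observed risk ratio |
|---|---|---|---|
| 0.05 | 0.08 + 0.92 × 0.05 = 0.126 | 0.04 + 0.96 × 0.05 = 0.088 | 0.70 |
| 0.10 | 0.08 + 0.092 = 0.172 | 0.04 + 0.096 = 0.136 | 0.79 |
| 0.15 | 0.08 + 0.138 = 0.218 | 0.04 + 0.144 = 0.184 | 0.84 |
| 0.25 | 0.08 + 0.230 = 0.310 | 0.04 + 0.240 = 0.280 | 0.90 |

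At f = 0.10, with 42 placebo and 84 fish-oil women (equal allocation assumed), false cases number 42 × 0.092 + 84 × 0.096 = 11.9. In the control arm 0.092/0.172 = 53% of counted cases are false. Missed true cases, if equally common in all arms, would move the ratio still closer to 1.

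**5. Preeclampsia.** Assume 2-10% of women falsely positive on pressure also meet the proteinuria criterion. A pressure error of 15-25% then becomes 0.15 × 0.02 = 0.3% to 0.25 × 0.10 = 2.5%. With the same 8% versus 4%, the observed ratio is 0.0429/0.0828 = 0.52 to 0.064/0.103 = 0.62. Dilution is far smaller than for gestational hypertension.

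**6. Power with a perfect definition.** Two-sided 5% test of two proportions, 42 versus 84, true risk ratio 0.50:

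| Control rate | Power | Women per arm for 80% power (two equal arms) |
|---|---|---|
| 5% | 14% | 906 |
| 8% | 18% | 553 |
| 10% | 21% | 435 |

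**The case against.** The strongest reply is that the trial could not detect such an effect anyway: power is 14-21% for a halving even with error-free classification, and these are exploratory analyses of secondary outcomes. This stands as a limit on the point. It does not remove it, because the stated use is to inform effect sizes for a later study, and there bias in the estimate matters as well as the p-value.

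A reader might also draw stronger conclusions that the documents do not support:

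- **That a real effect would be masked.** The rule dilutes an effect; sample size is the main reason none would be seen.
- **That preeclampsia is equally affected.** Proteinuria is also required, so the false-positive rates in step 3 do not carry over.
- **That any single reading, including one in labour, counts.** The article is silent on number and timing of readings. Those details could sit in a fuller document, and the three-reading figures rest on an assumed practice.
- **That a woman already at 150/95 who reaches 165/105 is a missed case.** Her pressure was raised at the start, so leaving her out of *gestational* hypertension is no error. The proposed definition would not count her either.
- **That the rates would clash with the 5-8% in the Discussion.** That figure only shows how common preeclampsia is relative to depression; the trial plans no comparison with it.

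**Conclusion.** The point holds for gestational hypertension: a stated case definition without an absolute level counts some women who stay in the normal range and misses some who become hypertensive. That much follows by arithmetic from the rule and a reference level.

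The size does not follow from the documents. The 7-29% on one late reading depends on the assumed pressures and variability. The shift from 0.50 to about 0.79-0.84 further assumes a true 8% versus 4%, 10-15% false positives equal across arms, and no missed cases. If the supplement shifted pressure within the normal range, false positives would not be equal, and the rule would register that shift as a change in disease.

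For preeclampsia the inherited missed cases remain, with a much lower false-positive rate. The primary outcome is untouched. The definition is worth correcting, but it does not threaten the trial's main conclusion.

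**What to change.** In Secondary Outcomes, for the analysis only:

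- define gestational hypertension by an absolute level (for example systolic ≥140 or diastolic ≥90 mm Hg, an illustrative choice for the investigators to settle), confirmed on a second reading and first met after a stated gestation;
- restrict it to women below that level at a named early-pregnancy reading, and report women already above it separately;
- use the same pressure criterion plus proteinuria for preeclampsia;
- keep the rise-only rule as a sensitivity analysis.

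This is a wording change to an outcome definition. It uses readings from the record already being abstracted and changes no treatment, visit or care decision. The cost is fewer counted events and wider intervals. It will not make the trial adequately powered for these outcomes.

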### Sample Size Considerations

We hypothesize that (i) fish oil supplementation will reduce the severity of depressive symptoms in the postpartum period among women at risk and that the (ii) EPA-rich fish oil (intervention #1) and DHA-rich fish oil (intervention #2) will be equally efficacious in reducing depressive symptoms. Our sample size calculation is based on the premise that fish oil supplementation of either the EPA-rich or DHA-rich dose will result in a 50 percent reduction in the mean BDI score at 6 weeks postpartum. Sample size calculations were generated in *nQuery Advisor *Version 6.01 based on data from a previous study conducted among the target population by one of the co-investigators, [name]. In that observational study, she observed a mean BDI score of 8.4 with a standard deviation of 6.4 among postpartum mothers at risk for depression. Assuming a significance level of 0.05, a one-way analysis of variance test, a variance of means (variance of the individual group means) of 3.920, a standard deviation of 6.4, and an effect size (the index of the separation expected among the observed means) of 0.0957, we will need to recruit 105 pregnant women (35 pregnant women in each of the three groups) to have 80% power to detect at least one group difference in the mean BDI score. We propose to recruit 126 pregnant women to account for the possibility of up to 10% study dropout and 10% initiating antidepressant therapy during the study period (to provide sufficient numbers for subgroup analyses).

Our decision to hypothesize a 50% reduction in the mean BDI score between intervention and control groups is based on results from published studies. Freeman and colleagues recently conducted two clinical trials[41,42] of omega-3 fatty acid supplementation and perinatal depression, using the EPDS as their primary measure of depressive symptomatology and reported a 51% and 41% reduction in EPDS score over an 8 week study period. A comparable study in a non-pregnant population demonstrated a similar effect size[43].

### Analysis Plan

We propose to recruit 126 women to examine the effect of a prenatal omega-3 fatty acid supplementation intervention on the risk of postpartum depressive symptoms at 6 weeks postpartum. Data will be prospectively collected via in-person interview, blood samples for serologic testing, and electronic medical chart abstraction. Information obtained from in-person interview and from chart abstraction will be initially completed by paper by a member of the research team and then transferred to a customized study database. The data files will be password protected and kept in a secure location on our network server. All statistical analyses will be performed using *Statistical Analysis Software (SAS) *Version 9.1 (SAS Institute, Inc., Cary, NC).

### Covariate Assessment

Other experiences of the participant that might influence depressive symptomatology must be considered as potential confounders. These include other exposures that occur during the prenatal and postpartum period. In addition to detailed information on the intervention and outcomes of interest, we will collect a detailed demographic, behavioral, dietary, and medical history from each participant at the time of study enrollment and review the participant's medical record and document any complications incurred during pregnancy.

### Descriptive Analyses

Once data have been collected, descriptive statistics (means, standard deviations, frequencies, proportions, and graphical displays) will be computed for all study variables. The distributions of outcome variables will be assessed to determine if distributional assumptions are valid. Decisions will be made at this time about the creation of category boundaries for certain continuous covariates, using well-established cut-points where appropriate. All analyses will be done on an intent-to-treat basis. Baseline analyses will be performed to determine if the three study groups are comparable or not with respect to various variables including age, parity, and body weight. If any of the baseline variables are shown to be different across the three groups, any outcome comparisons across the three groups will be adjusted for the potential confounding effect of these variables. In all analyses, we plan to control for possible confounders, and covariates that change the coefficient of interest by more than 10% will be retained in the final multivariable model.

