### Study Visits

As much as possible, the four study visits will be coordinated with the subjects' routine prenatal care or ultrasound appointments. Visit #1 will occur between 12 and 20 weeks' gestation. Full written informed consent will be obtained. Baseline demographic and past medical and obstetrical history data will be collected. The baseline BDI (Beck Depression Inventory) will be administered. After a 3-hour fast, subjects will have their blood drawn to measure their baseline omega-3 fatty acid and proinflammatory cytokine levels (IL-1β, IL-6, and TNF-α). Subjects will be given a 3 month supply of the study supplement at this visit. Subjects will be instructed to take three capsules twice daily with meals and to return all unused capsules to the research team at their next study visit.

The second study visit will take place between 26 and 28 weeks gestation. During this visit, the BDI will be completed and the MINI will be re-administered to assess for MDD, suicidal ideation and psychiatric co-morbidity. The subjects will return their prescriptions to the study staff and all unused capsules will be counted. A two month supply of the study supplement will be given to each subject.

The third study visit will take place between 34 and 36 weeks gestation. During this morning visit, the BDI will be completed and the MINI will be re-administered. In addition, a second fasting blood sample will be obtained to measure the participant's omega-3 fatty acid levels and proinflammatory cytokine levels (IL-1β, IL-6, and TNF-α). At this visit, a three-month supply will be dispensed in order to provide women with sufficient doses until the postpartum visit. Each participant will be provided with a packet containing sterile tubes for collection of cord blood. Participants will be instructed to bring this packet with them to the hospital when they present to the Labor and Delivery unit.

When the subject presents for delivery, clinical staff will be notified that the patient is a study participant. After delivery of the baby, cord blood will be collected and proinflammatory cytokine levels and fatty acid levels will be assayed (visit #4).

The final study visit will take place at the participant's 6 week postpartum check-up. During this visit, the BDI will be completed and the MINI will be re-administered. Participants will receive $20 and a parking voucher for each study visit that they attend.

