### Multivariable Analyses

To assess the effectiveness of a prenatal omega-3 fatty acid supplementation intervention in reducing the incidence and severity of depressive symptoms during pregnancy and up to 6 weeks postpartum, a one-way analysis of variance (ANOVA) with repeated measures will be used via the MIXED procedure in SAS. A one-way ANOVA has the advantage of testing whether there are any differences between the three groups with a single probability associated with the test. The hypothesis tested is that all groups have the same mean. We will have one within factor (time) and one between factor (supplement group). The ANOVA will allow us to assess the significance of the two main effects as well as if interaction is present, adjusting for potential confounding variables. Moreover, as a repeated measures design, it will allow us to use all four BDI assessments, which in turn will provide more detailed information about the trends over time than one or two assessments would. Lastly, we will be able to look at intermediate outcomes of interest, such as the effect of the prenatal omega-3 fatty acid supplementation intervention during pregnancy, using only the three BDI assessments performed during the prenatal period in our one-way ANOVA with repeated measures model.

Women who initiate antidepressant therapy during the study period will remain in the study for its duration. However, it will be necessary to take this change in treatment into account in our multivariable analyses. Thus, in addition to the above mentioned analyses, we will also perform a subgroup analysis among those who were not taking antidepressants during the study period. We will also test whether therapy could be a confounder or effect modifier of the effect of fish oil supplementation on depressive symptomtaology over the entire study cohort.

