All multivariable analyses will be performed using the MIXED procedure in SAS, as this procedure allows for missing data. While the research team will make every effort to collect data from all participants at all four time points during the study period, it is possible that a participant might miss one or two study visits. The methodological approach chosen for this proposal allows for some flexibility with the analyses performed. For example, comparisons will be drawn between baseline and 6 week postpartum BDI scores solely, as well as after taking into account the assessments drawn at 26-28 and 34-36 weeks gestation. Unlike the general linear models (GLM) procedure in SAS, the MIXED procedure does not remove all data for any subject that does not have complete data. Rather, all study participants are retained in the analysis and all available information is used.

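### Two data-driven rules choose the covariates for the outcome comparisons, and baseline BDI is not pre-specified as a covariate for the 6-week BDI

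*Protocol article*

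**What the plan says.** All references are to the protocol article.

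- **Descriptive Analyses, imbalance rule.** "Baseline analyses will be performed to determine if the three study groups are comparable or not", with age, parity and body weight given as examples. Then: "If any of the baseline variables are shown to be different across the three groups, any outcome comparisons across the three groups will be adjusted". No test, threshold or margin is stated.
- **Descriptive Analyses, change-in-coefficient rule.** The next sentence applies to all analyses: "covariates that change the coefficient of interest by more than 10% will be retained in the final multivariable model". It does not depend on the imbalance rule.
- **Study Visits, visit 1.** "The baseline BDI (Beck Depression Inventory) will be administered". The score is therefore available for every randomised woman who attends that visit.
- **Multivariable Analyses.** Baseline BDI enters as one of the repeated responses in a mixed model with group, time and their interaction: "it will allow us to use all four BDI assessments". The same section adds that "comparisons will be drawn between baseline and 6 week postpartum BDI scores solely", as well as comparisons that use the two intermediate visits.
- **Sample Size Considerations.** The trial is sized on a one-way analysis of variance without covariates, "to have 80% power to detect at least one group difference in the mean BDI score".

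The article nowhere names baseline BDI as a covariate, and it gives no correlation between baseline and 6-week BDI.

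**The concern.** In a randomised trial, a baseline difference between arms arises by chance. What makes a covariate worth adjusting for is how well it predicts the outcome, and neither rule selects on that as such. The imbalance rule looks only at the difference between arms. The 10% rule responds to the product of chance imbalance and predictive slope, relative to the estimated effect, so it too varies from one realised allocation to the next.

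Two things are at stake. The first is precision: baseline BDI is the same instrument measured earlier in the same women, and the trial is sized at only 80% power. The second is pre-specification: the model behind the main result is settled after outcome data are seen, and the second rule uses the treatment coefficient itself to settle it.

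**Working it through.** **Inputs from Sample Size Considerations.** Control mean 8.4, SD 6.4, 50% reduction in each active arm (mean 4.2), alpha 0.05, 35 per arm. The correlation ρ between baseline and 6-week BDI is my assumption, taken over 0.2 to 0.7.

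**Step 1: reproduce the stated design.** The means 8.4, 4.2 and 4.2 average 5.6. Variance of means = (2.8² + 1.4² + 1.4²)/3 = 11.76/3 = 3.92. Effect size = 3.92/6.4² = 3.92/40.96 = 0.0957. Both match the article. Noncentrality λ = 105 × 0.0957 = 10.05, with 2 and 102 degrees of freedom, gives power 0.805. At 34 per arm power is 0.793, so 35 is the smallest size reaching 80%. The stated figure is reproduced.

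**Step 2: baseline BDI used only as a response.** With arm means free at every visit and complete data, the model's 6-week contrast is the raw difference in 6-week means. Its power is that of step 1, about 80.5%, whatever ρ is. If the baseline-to-6-week comparison is read as a change contrast, the SD becomes 6.4 × √(2(1 − ρ)).

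**Step 3: baseline BDI as a fixed covariate.** The residual SD becomes 6.4 × √(1 − ρ²), so λ = 10.05/(1 − ρ²), with one error degree of freedom fewer. At ρ = 0.5, for example, the SD is 5.54, λ is 13.40 and power is 0.908.

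| Assumed ρ | Raw 6-week contrast | Change contrast | Adjusted for baseline BDI | Gain over raw (points) |
|---|---|---|---|---|
| 0.2 | 0.805 | 0.591 | 0.822 | 1.7 |
| 0.3 | 0.805 | 0.653 | 0.843 | 3.8 |
| 0.4 | 0.805 | 0.725 | 0.872 | 6.7 |
| 0.5 | 0.805 | 0.805 | 0.908 | 10.3 |
| 0.6 | 0.805 | 0.888 | 0.947 | 14.2 |
| 0.7 | 0.805 | 0.960 | 0.981 | 17.6 |

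**Step 4: baseline BDI as a candidate under both rules.** Ten per cent of the 4.2-point effect is 0.42 points. Adjustment moves a given arm coefficient by an amount with SD of about ρ × 6.4 × √(2/35). At ρ = 0.5 this is 0.765, so the chance of a move beyond 0.42 is P(|Z| > 0.55), about 58%. I simulated a 6-week model at 35 per arm with 20,000 trials per ρ, bivariate normal scores, the imbalance rule read as a 5% F test, and a covariate kept if either arm coefficient moves by more than 10%.

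| Assumed ρ | Kept by the 10% rule | Power, both rules | Power, always adjusted |
|---|---|---|---|
| 0.3 | 54% | 0.833 | 0.839 |
| 0.5 | 79% | 0.901 | 0.908 |
| 0.7 | 89% | 0.974 | 0.981 |

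The loss against always adjusting is 0.6 to 0.7 points. With no treatment effect and ρ = 0.5, the two rules together reject 4.8% of the time. If only one given arm coefficient is watched, baseline BDI is kept in 37%, 58% and 69% of trials, and the loss is about 1 to 2.5 points.

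**The case against.** The strongest objection is that the plan does not rely on imbalance alone. The 10% rule applies to all analyses, and step 4 shows that it would retain baseline BDI in most trials if that score is a candidate, with little power lost. The mixed model and the baseline-to-6-week comparison also make use of the baseline score. Both points stand, and they rule out several stronger readings that a reader might infer:

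- **Baseline BDI is adjusted for only about 5% of the time.** This follows from the imbalance rule alone, read as a 5% significance test. The article states no test, and the 10% rule is a separate route into the model.
- **About 10 points of power are lost.** This needs ρ near 0.5, which the article does not give, and it needs baseline BDI to enter only as a response.
- **A sizeable chance imbalance in baseline BDI passes uncorrected into the result.** A carry-over large enough to matter would exceed 10% of the target effect, and the second rule would then retain baseline BDI if it is a candidate.
- **The error rate falls clearly below 5%.** With both rules in force it stays close to 5%.

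The objection does not settle the point. The rescue works only if baseline BDI is on the candidate list, and the article never says so. Its examples are age, parity and body weight, and a score already modelled as the first response is not naturally a covariate in the same model. The change contrast removes baseline differences, but in step 3 it is less powerful than covariate adjustment at every ρ examined, and less powerful than the raw contrast below ρ = 0.5. A separate analysis plan may say more, but the two rules are stated here as the plan.

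**Conclusion.** The point holds as a matter of pre-specification and precision. The covariate set for the outcome comparisons is chosen from the data by two rules, and baseline BDI is not fixed as a covariate.

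The size depends on how the text is read. If baseline BDI is only a response with free arm means at each visit, which is how Multivariable Analyses describes the repeated-measures model, the 6-week contrast gives up about 2 to 18 points of power for ρ from 0.2 to 0.7. If it is a candidate under the 10% rule, the loss is under about 1 point (about 1 to 2.5 if a single arm coefficient is watched), and the remaining problem is that the model is chosen after the data are seen.

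These figures assume 35 evaluable women per arm, the article's means and SD, normally distributed scores, complete data and an assumed ρ. The documents do not support a claim that the primary comparison usually goes unadjusted, or that its error rate is compromised.

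**What to change.** - Delete the sentence that ties adjustment to observed baseline differences, and present baseline characteristics by arm descriptively, without a verdict on comparability.
- State that the primary comparison of 6-week BDI between arms is adjusted for continuous baseline BDI in every case. Alternatively, keep baseline BDI as a response in the mixed model and constrain the baseline arm means to be equal.
- Move both the imbalance-based adjustment and the 10% change-in-coefficient selection to sensitivity analyses. Removing only the first would leave the primary model dependent on the data.
- Quote any expected gain in power as a range over the assumed correlation.

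The cost is a few sentences of analysis text and one degree of freedom. Baseline BDI is already collected at visit 1, so no further data or participants are needed.
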